### Participant allocation/randomisation

The participants will be allocated based on the inclusion criteria. They will be randomized to preformed Bioflx crown and preformed zirconia crown as the intervention group or preformed stainless steel crown as the control group by computer-generated numbers. The research co-investigator will carry out data collection, data entry, and data analysis and will be blinded to group allocation.

### Interventions

Total 72 primary teeth requiring crowns will be randomly distributed in three groups of 24 each. The allocation will be carried out using computer-generated numbers. After obtaining written informed consent, the subjects will be enrolled, and teeth will be assigned randomly to the groups for receiving the intervention or conventional preformed crowns.

Group 1: Preformed stainless steel crown: control group

(3M™ ESPE™)

The material for coronal build-up for this group is a preformed stainless-steel crown(the control group). An appropriate-sized preformed stainless-steel crown will be selected. Tooth preparation will be carried out with tapered bur (pyrax Dental Mani Diamond Burs TR-13C) to reduce occlusal surface up to 1 to 1.5 mm. The interproximal reduction will be made mesially and distally. The selected crown size will be checked and a trial fit will be done before cementation. It will require crimping pliers and the crown will be cemented using type 1 glass ionomer cement (GC Gold Label I/ Fuji I). The excess will be removed and proper occlusion will be checked.
^
8
^

Group 2: Preformed Bioflx crown

The Preformed Bioflx crown (
Kids-e-dental LLP [Limited Liability Partnership]) will be used in this group. A similar sized preformed crown will be selected. Tooth preparation will be carried out with a tapered diamond bur (pyrax Dental Mani Diamond Burs TR [Taper Round] -13C) for occlusal reduction by 1–1.5 mm, including the central groove. The proximal preparation will be around 0.5 mm to clear the contact area. Placement of the crown will be achieved by a snug fit followed by contouring using a How plier (GDC How Plier # Curved (3000/72).

Crown cementation will be carried out using a glass ionomer type I (GC Gold Label I/ Fuji I) and removal of excess cement using floss or explorer.

Group 3: Preformed zirconia crown

The material for crown restoration for this group is the preformed zirconia crown (Kids-e-dental LLP). A diamond bur will reduce the occlusal surface by 1.5–2 mm. Interproximally, contacts will be prepared with a tapered fissure bur. About 1–2 mm subgingival preparation will be performed. The selected crown will be placed and checked. The passive fit of the crown will be assessed and will be luted with dual cure resin cement (Prevest Fusion Ultra D/C / Dual Cure Resin). Consistent firm finger pressure will be applied during cementation. Crown placement will be assessed.
^
8
^

### Comparison

We will compare the control group (stainless steel crown) with Bioflx and Zirconia crowns on basis of their clinical performance and parental satisfaction.

### Outcome measures

Preformed esthetic crowns and preformed stainless steel crown outcomes will be assessed by the research co-investigator at different time intervals of zero, three months, six months, and 12 months follow-up based on clinical performance, and child and parental satisfaction based on three evaluation criteria, which include clinical, clinicians’ and parental satisfaction. The child and parental satisfaction score will be measured using a questionnaire-based five-point rating Likert’s scale.
^
1
^ Outcome will be evaluated based on durability, flexibility, self adaptability. Bioflx crowns will be a smart option for pediatric tooth-coloured crowns.

### Data collection

The questionnaire for assessing child and parental satisfaction score consists of four main categories in satisfaction rating of esthetic characteristics.
^
1
^ These categories are size, shape, color, and stain. The response format will be a five-point Likert scale, ranging from not at all satisfied, with a score of 1, to very much satisfied, with a score of 5.

Another questionnaire scale based on parental ratings of the impact of treatment on their children
^
9
^ consists of five categories, including 1) The oral health of the child improved after crowns; 2) Parents concern about appearance before crowns; 3) The child avoided smiling before crowns; 4) Child smiling after crowns; 5) Crowns have improved the appearance of the child’s teeth. The response format will be a five-point Likert scale, ranging from not at all (score of 1) to very much (score of 5).
^
7
^
^,^
^
9
^

### Data entry and storage

The research co-investigator will carry out data entry. The principal investigator will review the data entered for discrepancies such as entry errors, enrolment errors, etc. The data entry errors will be checked by a co-investigator by randomly selecting data sheets.

### Data analysis and statistical plan

Statistical analysis will be done using general methodology; continuous variables will be summarized using tables of descriptive statistics: the number of patients with recorded observations, mean, standard deviation, median, minimum, and maximum. Categorical variables will be determined using counts and percentages. Descriptive statistics will be presented by diagnosis and all the results will be calculated using
RStudio Version: 2023.03.1+446 (RRID: SCR_000432) will be used. Comparison of continuous parameters between the three groups will be performed using an ANOVA test for quantitative data or Kruskal Wallis test for qualitative data. Categorical variables will be summarized using the frequencies and percentages and compared between the three groups.

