**Results:**

Bioflx crown will have better clinical as well as parental satisfaction among zirconia and stainless steel crowns.

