### Objectives

The objectives are as follows:
•To evaluate and compare the clinical performance of Bioflx, zirconia, and stainless steel crowns in primary dentition based on recurrent caries, gingival health, restoration failure, plaque accumulation, opposing tooth wear, and clinicians’ satisfaction at zero, three, six and 12 months follow up.•To assess the child and parental satisfaction of Bioflx, zirconia, and stainless steel crowns in primary dentition at zero, three, six, and 12 months.

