### Sample size

A sample size of children aged three- to seven-years-old will be selected and 72 primary teeth requiring crowns will be randomly distributed in three groups of 24, as follows:

$$N=\frac{{\left(Z_{\left(\alpha /2\right)}+Z_{\beta }\right)}^{2}\left(P_{1}\left(1-P_{1}\right)+P_{2}\left(1-P_{2}\right)\right)}{{\left(P_{2}-P_{1}\right)}^{2}}$$
(1)

$$Z_{\alpha /2}=\text{at 99\% (CI)}=2.576$$

Represents the desired level of statistical significance

$Z_{\beta }=1.28$
: Represents the desired power = 1.28 for 90%

*N* = Minimum samples required for each group

Where,

*P*
_1_ = Estimated proportion of study outcome (Child satisfaction % Experimental group) = 99.99% (Approximate to 100%)
(1)
^
1
^

*P*
_2_ = Estimated proportion of study outcome (Child satisfaction % Control group) = 53.33%
^
1
^

At a level of significance at 1% and power 90%

The minimum sample size required:

$$N={\left(2.576+1.28\right)}^{2}\;{\left(0.999\right)}^{*}\;\left(1-0.999\right)+{\left(0.533\right)}^{*}\;\left(1-0.533\right)/0.466=22\;\mathrm{per}\;\text{group}$$

Considering 10% dropout=2

Samples required22+2=24each

$$\text{Total samples required for three groups}=3^{*}N=72\;\text{total}$$

Mathew
*et al.,* showed the difference between the two proportions of child satisfaction (%) as the primary variable
(1)
^
1
^

P1(for the experimental group) = 100% (considered as 99.999% approx to 100%) and for the control group (53.333%). We considered a clinically significant margin of difference at 46.666%. Also, we considered the assumption for statistical significance, the highest statistical significance level of 1% alpha value with power (1-beta) at 90%.

We use the test statistics of two independent proportion sample size calculations with the given formula samples for taking the minimum samples required in each group.

Calculated with 22 samples required in each group, adding 10% of dropout = 2. A total of 22 + 2 = 24 samples are required in each group, with a sample size of 72 children distributed in three groups.

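### The trial is sized on one test of child satisfaction at 1% alpha, but the protocol never fixes that test's visit, cut-off or crown contrast, and no planned analysis is tied to it

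*Protocol article*

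**What the plan says.** **Sizing.** The Sample size section uses a formula for two independent proportions. The control figure is "Estimated proportion of study outcome (Child satisfaction % Control group) = 53.33"%, and the experimental figure is set at practically 100%. The error rates are given as "the highest statistical significance level of 1% alpha value with power (1-beta) at 90" per cent, with a normal quantile of 2.576, so the test is two-sided. The result is 22 per group, raised to 24 for dropout, or 72 in three groups. The proportion is called the primary variable in the sentence about the cited study.

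**Outcomes and visits.** The second objective reads "To assess the child and parental satisfaction of Bioflx, zirconia, and stainless steel crowns in primary dentition at zero, three, six, and 12 months". The first objective puts clinical performance and clinicians' satisfaction on the same four-visit schedule. Outcome measures repeats assessment "at different time intervals of zero, three months, six months, and 12 months follow-up". Neither section ranks an outcome or a visit. The abstract's Methods paragraph lists seven outcomes: recurrent caries, plaque, restoration failure, gingival status, opposing tooth wear, clinicians' satisfaction and parental satisfaction. The Comparison section names clinical performance and parental satisfaction. Neither list contains child satisfaction.

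**Analysis.** The Data analysis and statistical plan section says "Comparison of continuous parameters between the three groups will be performed using an ANOVA test for quantitative data or Kruskal Wallis test", and that categorical variables are also compared between the three groups. It names no deciding outcome or visit and no significance level.

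**Expected claim.** The abstract's Results paragraph anticipates that "Bioflx crown will have better clinical as well as parental satisfaction among zirconia and stainless steel crowns".

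**The concern.** A 1% error rate belongs to a specified test. Here the sample size rests on one test, and the rest of the protocol describes a different and wider set of comparisons. A reader cannot tell which result would make the trial positive. It could be satisfaction at month 0 or at month 12, Bioflx or zirconia against stainless steel, or a clinical outcome.

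Two things are at stake. First, the 1% level chosen for sizing may not describe the error rate of the trial's conclusion. Second, results can disagree: one crown may look better on satisfaction early and another on plaque late. With no deciding test fixed beforehand, the choice between them can be made after the data are seen.

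**Working it through.** **1. Reproduce the plan's figure.** Inputs from Sample size: P1 = 0.9999, P2 = 0.5333, z = 2.576 and 1.28.

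- Mean proportion: (0.9999 + 0.5333)/2 = 0.7666.
- Pooled variance term: 2 × 0.7666 × 0.2334 = 0.3578.
- Separate variance term: 0.9999 × 0.0001 + 0.5333 × 0.4667 = 0.2490.
- Squared difference: 0.4666² = 0.2177.
- N = (2.576 × √0.3578 + 1.28 × √0.2490)² / 0.2177 = 21.8, so 22 per group.

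The stated 22 is therefore the size for one two-sided 1% comparison of two proportions. The formula as printed uses only the separate variances and gives 3.856² × 0.2490 / 0.2177 = 17.0. The 22 matches the pooled version of the same test. Either way, N is for a single test.

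**2. Is that test specified anywhere?**

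| Element | What the protocol gives |
|---|---|
| Outcome | Proportion of satisfied children, in Sample size only |
| Cut-off | None; Data collection gives a scale from 1 to 5 |
| Visit | None; four visits of equal standing |
| Contrast | An unnamed experimental group against control. Two crowns are experimental, and the Discussion describes the cited study as zirconia against stainless steel |
| Matching analysis | None; three-group tests in general terms |

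**3. What happens to 1% if several comparisons can carry the conclusion?** The protocol does not fix the number of tests, so two families are taken as assumptions. Each test is a three-group comparison at 1% with no true difference. For k independent tests, the chance of at least one false positive is 1 − 0.99^k. For correlated tests it was simulated, with each test a chi-square on 2 degrees of freedom and equal correlation between tests.

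| Family (assumed) | k | Correlation 0.8 | 0.5 | 0 |
|---|---|---|---|---|
| One satisfaction score, four visits | 4 | 2.6% to 2.7% | 3.6% | 1 − 0.99^4 = 3.9% |
| Seven outcomes in the abstract, four visits | 7 × 4 = 28 | 7.4% | 15.5% | 1 − 0.99^28 = 24.5% |

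**4. Correction for rare events.** The second row treats every test as having exactly 1% size. Recurrent caries and restoration failure may be too rare for that. With 24 per group and an assumed 5% event rate, a nominal 1% three-group Pearson test has a true size of about 0.22%; at a 2% event rate it is about 0.01%. If those two outcomes at four visits (8 tests) run at 0.22%, the independent case becomes 1 − 0.99^20 × 0.9978^8 = 19.6%. So 25% is an upper figure.

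**The case against.** **The statistical analysis plan is not shown.** It may hold a multiplicity rule, and a journal article need not print one. This stands as far as the technique goes, and no point is made of a missing adjustment method. It does not cover the deciding outcome, cut-off, visit and contrast. The sample size depends on these, so they are protocol-level choices.

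**An outcome is named.** A reader might infer that the protocol has no primary outcome at all. The document does not support that. Sample size treats child satisfaction as the study outcome, defines both proportions for it and sets a clinically significant margin on it. What is missing is the rest of its definition and an analysis that uses it.

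**Per-item, per-visit testing is not stated.** A reader might count every listed criterion: 9 clinical, 7 clinician, 4 aesthetic and 5 impact items make 25, and at four visits 100 tests. From that comes a false-positive rate of about 31% (correlation 0.5) to 63% (independent). The document does not support that count. The analysis section does not say that single items or single visits are tested, and Outcome measures speaks of a satisfaction score. Stain resistance appears in two lists, two impact items concern the time before crowns, and rare binary items add little. For the same reasons no single multiple of the stated alpha, such as 10 to 31 times, can be attached to this protocol.

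**The expected claim is a placeholder.** It is written for a study not yet begun, it joins clinical and satisfaction benefit, and the Conclusions expect similar results for all groups. This is fair. The sentence does not show that any one significant item would be called success. It does show that nothing says which result must be positive.

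**Conclusion.** The point holds in a limited form. The trial is sized for one two-group test of child satisfaction at two-sided 1%. The protocol does not fix that test's visit, cut-off or contrast, leaves the outcome out of two of its own lists of what is compared, and plans no analysis tied to it. Followed as written, the 1% level does not protect the trial's conclusion.

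The size depends on assumptions the document does not settle: 1% per test, correlation between 0.8 and 0, and the number of tests. Under them the false-positive chance is about 2.6% to 4% in the mildest case (one score at four visits). It is about 7% to 25% for the abstract's seven outcomes at four visits, the top being an upper figure. The analysis section gives no level, so 1% per test is itself carried over from the sizing. The change should be made; the study has not started.

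**What to change.** In Sample size, Outcome measures and the analysis section, name one deciding test:

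- **Outcome:** the proportion of satisfied children used for sizing, with its cut on the five-point scale defined.
- **Visit:** one, for example 12 months.
- **Contrast:** one named crown against stainless steel, for example Bioflx.
- **Test:** a two-proportion or exact test at two-sided 1%.

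If a mean satisfaction score is preferred, N must be justified again. The protocol gives no standard deviation or mean difference, so the power of 24 per group for a score cannot be derived from it.

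Test any further confirmatory contrast on the same outcome in a fixed sequence, each at 1% and only if the one before is significant. This leaves the first test, and so the sample size, unchanged. Splitting alpha over two crown-versus-control tests instead (0.005 each) would need 25 per group for 90% power; power would be 84.6% with 22 and 88.8% with 24.

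Report all other outcomes, items and visits as secondary or exploratory estimates with confidence intervals, and align the outcome lists in the abstract and the Comparison section with this choice.

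The cost is a few sentences, with no extra patients, visits or data. The downside is that nominally significant secondary or early-visit results can no longer be presented as proof of superiority.

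### One-way group tests are named for outcomes measured at four visits, with no primary visit and no way of handling repeated readings on a tooth

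*Protocol article*

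**What the plan says.** All places are in the protocol article.

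- **Objectives.** The clinical objective ends with "clinicians’ satisfaction at zero, three, six and 12 months follow up". The second objective is "To assess the child and parental satisfaction of Bioflx, zirconia, and stainless steel crowns in primary dentition at zero, three, six, and 12 months".
- **Outcome measures.** Outcomes are to be "assessed by the research co-investigator at different time intervals of zero, three months, six months, and 12 months follow-up".
- **Data analysis and statistical plan.** The between-group method is "Comparison of continuous parameters between the three groups will be performed using an ANOVA test for quantitative data or Kruskal Wallis test for qualitative data". For categorical outcomes: "Categorical variables will be summarized using the frequencies and percentages and compared between the three groups". No visit, visit term, repeated-measures method or primary time point appears, and no test level is given.
- **Sample size.** The trial is sized on a two-group difference in the proportion of satisfied children, "At a level of significance at 1% and power 90" per cent. No visit is attached to that proportion.
- **Study setting and population** and **Recruitment and consent.** A child may contribute several teeth, and children with more than one decayed tooth needing a crown are to be selected.

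**The concern.** ANOVA and Kruskal-Wallis, as named, compare independent groups on one value per unit. The data will hold up to four values per tooth for each outcome. The article does not say how four values become one test, so several analyses remain open until the data are seen.

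Two things are at stake. The first is the error rate: if every visit is tested and no visit is primary, any one of four results can be reported as the finding. The second is precision: with 24 teeth per group, a test at one visit ignores the other readings and drops a tooth that missed that visit even when its other readings exist. A set of separate group tests also gives no direct estimate of whether the crowns diverge over 12 months.

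**Working it through.** **1. The plan's own figure.** Inputs from Sample size: z = 2.576 and 1.28, P1 about 0.9999, P2 = 0.5333. The usual two-proportion formula with pooled variance under the null gives:

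- mean proportion (0.9999 + 0.5333)/2 = 0.7666
- 2.576 × √(2 × 0.7666 × 0.2334) = 1.541
- 1.28 × √(0.9999 × 0.0001 + 0.5333 × 0.4667) = 0.639
- (1.541 + 0.639)² / 0.4666² = 21.8, so 22 per group.

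The stated 22 is reproduced. The formula as printed gives about 17 (3.856² × 0.2499 / 0.466² = 17.1). That is a separate matter and does not bear on this point. What matters here is that the calculation covers one comparison at no stated visit.

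**2. Assumption.** The documents give no between-visit correlation ρ. A range of 0.2 to 0.8 is used, equal for every pair of visits.

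**3. False positives.** Simulation with no true difference: 3 groups × 24 teeth × 4 visits, normal data, no trend over time, no missing visits, teeth independent of each other, 20,000 runs. Entries are rejection rates of the one-way ANOVA.

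| ρ | Any of four visits, 5% | Any of four visits, 1% | Rows stacked, 5% | Rows stacked, 1% |
|---|---|---|---|---|
| 0.2 | 0.180 | 0.039 | 0.154 | 0.056 |
| 0.3 | 0.176 | 0.041 | 0.204 | 0.087 |
| 0.5 | 0.156 | 0.035 | 0.301 | 0.159 |
| 0.7 | 0.134 | 0.031 | 0.387 | 0.232 |
| 0.8 | 0.118 | 0.028 | 0.421 | 0.265 |

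For reference, four independent tests would give 1 − 0.95⁴ = 0.185 and 1 − 0.99⁴ = 0.039. The 0.041 in the table is within simulation error of the latter. A test at 12 months alone, or on one mean per tooth, stayed at about 0.05 and 0.01 throughout. Kruskal-Wallis on stacked rows behaved like ANOVA (0.15 to 0.42 at nominal 5%, 2,000 runs).

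**4. Precision.** For an effect constant over the three post-placement visits, the variance of their average relative to one visit is (1 + 2ρ)/3.

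| ρ | Variance ratio | Information lost by using one visit | Equivalent extra teeth |
|---|---|---|---|
| 0.3 | 1.6/3 = 0.533 | 47% | 1/0.533 = 1.88, so 88% |
| 0.5 | 2.0/3 = 0.667 | 33% | 1/0.667 = 1.50, so 50% |
| 0.7 | 2.4/3 = 0.800 | 20% | 1/0.800 = 1.25, so 25% |

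One visit would lose more than half only if (1 + 2ρ)/3 < 0.5, that is ρ below 0.25.

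**The case against.** **The named tests can be valid.** ANOVA at one pre-named visit, or on a per-tooth mean or change, fits the wording and holds its level. An ANOVA on change scores would also address divergence. This stands. The defect is that no such choice is fixed, not that ANOVA must fail.

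**This is a condensed article, and an analysis plan may exist.** Handling of visits and missed readings is often left to such a plan. This stands in part: a separate plan could settle the point. But the article does more than stay silent. Under a heading that calls itself the statistical plan, it picks the between-group tests, and those tests do not match the four-visit design in its own objectives.

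**Two stronger readings are tempting.**

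- A reader might infer that visits will be stacked and each tooth counted four times. The text does not exclude this, but nowhere states it. The 9% to 23% at nominal 1% (ρ 0.3 to 0.7) shows what stacking would cost and is not a property of the plan.
- A reader might infer that testing single visits throws away most of the follow-up. The loss is 20% to 47% at ρ 0.3 to 0.7. Tests at all four visits, taken together, use all the data; their cost is multiplicity.

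**A mixed model is not free.** This also stands. The precision gain needs a constant effect and equal correlations. Expected satisfaction near 100% in the experimental group may make an ordinal model separate. A random effect for tooth alone would leave teeth in the same child treated as independent.

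**Conclusion.** The point holds in limited form. The article names one-way between-group tests for outcomes measured four times and fixes neither a primary visit nor a method for within-tooth correlation.

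On the natural reading, with a test at each visit, the chance of at least one false positive per outcome is about 12% to 18% at nominal 5% and 3% to 4% at nominal 1%. Each such test also forgoes a substantial part, though not most, of the post-placement information.

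These figures rest on assumed exchangeable correlations (0.2 to 0.8 for the error rates, 0.3 to 0.7 for precision), complete normal data and, for precision, a constant crown effect. They cover one outcome at a time; multiplicity across the many outcomes is additional. The change should be made because it is cheap and the study is described as not yet started, but nothing here shows that the stated tests will give a wrong answer.

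**What to change.** In the data analysis section:

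1. Name one primary contrast per outcome, for example crown group at 12 months.
2. Estimate it from one repeated-measures model with group, visit and group-by-visit as fixed effects, and random effects for child and for tooth within child.
3. Use a linear model for index scores. For Likert and satisfaction outcomes, including the binary satisfaction proportion behind the sample size, use an ordinal or binary mixed model, or GEE clustered on child. State in advance a penalised or simpler fallback if responses separate.
4. Report the average over 3, 6 and 12 months as a secondary contrast, with confidence intervals for both.

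**Cost.** Revised wording and a modest amount of R code, R already being the planned software; no new data.

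**Downsides to state.** Likelihood-based models assume that missed visits are missing at random, and standard GEE needs a stronger assumption. The averaged contrast dilutes an effect that grows over time, which is why it is secondary. Ordinal models may be unstable with 24 teeth per group.

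If the investigators prefer the named tests, the minimum change is to fix one primary visit or one per-tooth summary per outcome and label the other visits as secondary. That restores the error rate but not the lost precision, and it leaves teeth from the same child still to be handled.

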## Methods

### Study design

A randomized controlled trial with a parallel group will be the research design for the study. Total 72 primary teeth requiring crowns will be randomly distributed in three groups of 24 each. The allocation will be carried out using computer-generated numbers. After obtaining written informed consent, the subjects will be enrolled, and teeth will be assigned randomly to the groups for receiving the intervention or conventional preformed crowns. The study adheres to the protocol following the Standard Protocol Items: Recommendations for Interventional Trials (SPIRIT) guidelines.
^
7
^ The allocation of participants and flow diagram for study participants is shown in
Figure 1.

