*et al*. (2021) performed a randomized clinical trial to determine the expectancy of survival rate in one year after endodontic treatment in deciduous molars having restoration with stainless steel and bulk-fill composite crowns. Samples were evaluated and randomized at one, three, six, and 12 months of follow up. The survival rate after one year for the stainless-steel crown was 88% and the bulk fill composite was 75%. In intention-to-treat analysis, the success rate of the bulk fill crown was 86.7% and the stainless steel crown was 82.6%. Both the children and their parents were satisfied with the treatments.
^
10
^

Another similar study by Murali
*et al*. (2022) compared stainless-steel and zirconia crowns. At follow-up, these crowns were evaluated based on proximal contacts, retention, plaque accumulation, marginal integrity, gingival inflammation, and opposing tooth wear. The author concluded that the success rate of zirconia was 93.5% and for stainless steel full coverage restoration was 96.7%. In their statistical analyses, it was observed that there was no significance between the groups, and the preformed stainless steel and zirconia crowns showed good results but zirconia was preferred aesthetically.
^
8
^

The Bioflx crown has been introduced in pediatric practice as a synthetic crown that will provide better adaptation, durability, and ease of handling with improved aesthetic properties compared to conventional crowns. The limitations of this study will be that long-term follow up will be required for more detailed clinical observation and larger sample size will provide more rigorous results.

The study will help improve the properties of conventional crowns and the Bioflx crown may provide a promising result in terms of the clinician’s and parental satisfaction as aesthetic is a prime concern for parents and children in this era.

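### With 24 teeth per arm, a non-significant comparison of crown failures cannot support similar clinical performance, so crown failure should be analysed by estimation with intervals

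*Protocol article*

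**What the plan says.** The first item under Objectives is "To evaluate and compare the clinical performance of Bioflx, zirconia, and stainless steel crowns in primary dentition", and the features it lists include restoration failure and recurrent caries.

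Study design fixes the size: "Total 72 primary teeth requiring crowns will be randomly distributed in three groups of 24 each". The Sample size section derives this from child satisfaction only, taking the experimental proportion as "100% (considered as 99.999% approx to 100%) and for the control group (53.333"%). It states "At a level of significance at 1% and power 90"%, with attrition handled as "Considering 10% dropout=2". No calculation is given for a clinical outcome.

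In Data analysis and statistical plan, continuous measures get ANOVA or Kruskal-Wallis. For the rest: "Categorical variables will be summarized using the frequencies and percentages and compared between the three groups". No test for categorical data is named.

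The Discussion supplies failure rates. For one study of two of this trial's crown types it reports that "the success rate of zirconia was 93.5% and for stainless steel full coverage restoration was 96.7"%. For another trial it reports one-year survival of 88% for steel crowns and 75% for bulk-fill composite, with intention-to-treat success of 82.6% and 86.7%.

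The closing Conclusions section expects results in all groups, Bioflx included, to resemble those in the literature. The Abstract's conclusion already accepts Bioflx as an alternative restoration, although the study has not started.

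**The concern.** Crown failures are few at the cited rates, and 24 teeth per arm were chosen to detect a 46.7-point difference in satisfaction. A comparison of failure percentages at that size will usually be non-significant, even if one crown type fails several times as often as another. The article's expectation of similarity, and its conclusion that a new crown is usable as an alternative, are the statements that such a null result would seem to confirm. What is at stake is the answer to the failure part of the first objective. The trial can say how high a failure rate its data exclude, but the analysis as described does not ask for that.

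**Working it through.** **The plan's own figure.** With p1 = 0.999, p2 = 0.5333, two-sided alpha 1% and power 90%, the pooled-variance formula is

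n = [z(α/2)·√(2·p̄·(1−p̄)) + z(β)·√(p1(1−p1) + p2(1−p2))]² / (p1−p2)²

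Here p̄ = 0.766, so n = [2.576 × 0.5986 + 1.28 × 0.4999]² / 0.4657² ≈ 21.9, or 22 per group. This reproduces the stated 22, and adding 2 gives 24. The unpooled formula printed in the protocol gives 3.856² × 0.2499 / 0.466² = 17.1, so 18; that is a separate matter. The 24 per arm and the 90% power belong to satisfaction.

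**Expected failures per arm of 24.**
- First cited study: steel 24 × 0.033 = 0.8; zirconia 24 × 0.065 = 1.6. The chance of no failure at all is 0.967^24 = 45% and 0.935^24 = 20%.
- Second cited trial, steel: 24 × 0.12 = 2.9 (one-year survival) or 24 × 0.174 = 4.2 (intention to treat).

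**What a two-arm Fisher test needs, 24 v 24.** When one arm has no failures and the other has k, the two-sided p = 2·C(24,k)/C(48,k).
- k = 4: 2 × 10,626 / 194,580 = 0.109
- k = 5: 2 × 42,504 / 1,712,304 = 0.0496
- k = 7: 2 × 346,104 / 73,629,072 = 0.0094

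So 0 v 4 (0% v 17%) is not significant at 5%. With one failure in the better arm, the other needs 7 of 24 (29%) at 5%.

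**Power.** Sum Bin(a; 24, fA) × Bin(b; 24, fB) over all tables with p ≤ α. The document names no test, so uncorrected Pearson is shown beside Fisher.

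| Failure rates | Origin | Fisher, 5% | Fisher, 1% | Pearson, 5% |
|---|---|---|---|---|
| 3.3% v 6.5% | first cited study | 0.8% | 0.03% | 3.3% |
| 12% v 25% | second cited trial, survival | 14% | 3% | 22% |
| 17.4% v 13.3% | second cited trial, intention to treat | 3.5% | 0.5% | 7.1% |
| 3.3% v 15% | assumed | 15% | 3% | 28% |
| 3.3% v 20% | assumed | 32% | 9% | 47% |
| 3.3% v 25% | assumed | 50% | 20% | 65% |
| 3.3% v 35% | assumed | 80% | 50% | 88% |

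A three-group exact test, with steel at 3.3% and zirconia at 6.5%, has about 2% power at the 5% level if Bioflx fails at 3.3% or 6.5%, 34% if at 20%, and 83% if at 35%. With 22 evaluable teeth per arm, the two-arm Fisher figures at 5% fall to 0.6% (3.3% v 6.5%), 27% (v 20%) and 75% (v 35%). Detecting 3.3% v 6.5% with 80% power at the 5% level would need 714 teeth per arm.

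**What intervals would say.** For no failures in n teeth, the exact two-sided 95% upper limit is 1 − 0.025^(1/n): 14.2% for n = 24 and 15.4% for n = 22. The Newcombe 95% interval for a difference is about −13 to +22 points for 1/24 v 2/24, and about −14 to +14 points for 0/24 v 0/24.

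**The case against.** Several objections carry weight.

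- **Testing as the only inference.** A reader might infer that the plan commits to a significance test and nothing else. It does not: it says the groups will be compared, names no categorical test, and also promises percentages per arm. Intervals may be specified in an analysis plan that is not shown. The absence of a named interval is therefore not the point. The point is that the stated objective, the sizing and the anticipated conclusion do not fit together.
- **A null result whatever happens.** A reader might also infer that the comparison cannot detect anything. That fails on the figures: Fisher power at 5% is 50% when one arm fails at 25% and 98% when it fails at 50%, against 3.3%.
- **Choice of rates.** The second cited trial has higher steel failure rates and a one-year horizon that matches this trial. Using them raises power, but only to 14% (Fisher) or 22% (Pearson). Composite is not an arm here.
- **Power and alpha.** The protocol already ties its 90% power to child satisfaction and does not claim it for clinical outcomes. The 1% level is likewise set only in that calculation, so the 5% figures are the fairer ones here. Low power for outcomes that did not set the sample size is ordinary, and the Discussion concedes generally that a larger sample would be more rigorous.
- **Scope.** Clinical performance also covers gingival and plaque indices and tooth wear, for which ANOVA or Kruskal-Wallis may serve. No recording scale is given for retention, fracture or recurrent caries, so treating them as yes/no is an assumption.
- **Predicted misreading.** The expectation of similar results is drawn from the literature. The article does not say that a non-significant test will be taken as proof of similarity.

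None of this makes a null comparison of failures informative about similarity.

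**Conclusion.** The concern holds for failure-type outcomes: at 24 teeth per arm, a non-significant comparison cannot support comparable performance or the use of Bioflx as an alternative. Fisher power at 5% is 0.8% and 14% at the two sets of rates above (failure 3.3% v 6.5%; survival 88% v 75%), and 32% for a roughly six-fold rise from 3.3% to 20%. It reaches about 80% only near 35% failure in one arm. An arm with no failures still leaves rates up to 14.2% open.

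These figures assume yes/no outcomes, one independent tooth per child and no dropout. Dropout lowers power. Study setting and population and Recruitment and consent both allow several teeth per child; positive correlation within a child would make the 14.2% limit too optimistic, while the effect on a difference depends on how a child's teeth are spread over the arms.

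The documents do not support the claims that the plan relies on testing alone or that the comparison would miss any difference. This is a cheap improvement to the analysis and its reporting, not a fault that invalidates the design.

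**What to change.** For retention or failure, fracture and recurrent caries, where recorded as yes/no, make estimation the main analysis:

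- Report failures and teeth per arm at 12 months, with exact 95% intervals.
- Report each pairwise crown difference with a score or exact 95% interval.
- If any child contributes more than one tooth, use intervals that account for clustering by child.
- State that the conclusion on clinical performance will rest on the failure rates and differences that the intervals exclude, and that a non-significant comparison will not be reported as similar performance.

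This takes a few sentences in the analysis section and no extra children or visits. The price is that the clinical conclusion becomes visibly less certain.
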